## Abstract

**Background:**

Hip dysplasia is one of the most common causes of hip arthritis. Its incidence is estimated to be between 3.6 and 12.8% (Canadian Institute for Health Information, Hip and knee replacements in Canada, 2017–2018: Canadian joint replacement registry annual report, 2019; Jacobsen and Sonne-Holm, Rheumatology 44:211–8, 2004). The Periacetabular Osteotomy (PAO) has been used successfully for over 30 years (Gosvig et al., J Bone Joint Surg Am 92:1162–9, 2010), but some patients continue to exhibit symptoms post-surgery (Wyles et al., Clin Orthop Relat Res 475:336–50, 2017). A hip arthroscopy, performed using a small camera, allows surgeons to address torn cartilage inside the hip joint. Although both procedures are considered standard of care treatment options, it is unknown whether the addition of hip arthroscopy improves patient outcomes compared to a PAO alone. To delay or prevent future joint replacement surgeries, joint preservation surgery is recommended for eligible patients. While previous studies found an added cost to perform hip arthroscopies, the cost-effectiveness to Canadian Health care system is not known.

**Methods:**

Patients randomized to the experimental group will undergo central compartment hip arthroscopy prior to completion of the PAO. Patients randomized to the control group will undergo isolated PAO. Patient-reported quality of life will be the primary outcome used for comparison between the two treatment groups as measured by The International Hip Outcome Tool (iHOT-33) (Saberi Hosnijeh et al., Arthritis Rheum 69:86–93, 2017). Secondary outcomes will include the four-square step test and sit-to-stand (validated in patients with pre-arthritic hip pain) and hip-specific symptoms and impairment using the HOOS; global health assessment will be compared using the PROMIS Global 10 Score; health status will be assessed using the EQ-5D-5L and EQ VAS questionnaires (Ganz et al., Clin Orthop Relat Res 466:264–72, 2008) pre- and post-operatively. In addition, operative time, hospital length of stay, adverse events, and health services utilization will be collected. A sub-group of patients (26 in each group) will receive a T1rho MRI before and after surgery to study changes in cartilage quality over time. A cost-utility analysis will be performed to compare costs and quality-adjusted life years (QALYs) associated with the intervention.

**Discussion:**

We hypothesize that (1) concomitant hip arthroscopy at the time of PAO to address central compartment pathology will result in clinically important improvements in patient-reported outcome measures (PROMs) versus PAO alone, that (2) additional costs associated with hip arthroscopy will be offset by greater clinical improvements in this group, and that (3) combined hip arthroscopy and PAO will prove to be a cost-effective procedure.

**Trial registration:**

ClinicalTrials.gov NCT03481010. Registered on 6 March 2020. Protocol version: version 3.

## Background

### Problem to be addressed

In the fiscal years 2017–2018, 58,492 hip replacements were performed in Canada, which reflects a 17.4% increase over the preceding 5 years [1]. More than $1 billion is currently spent annually performing joint replacement surgeries as a result of secondary osteoarthritis (OA) [1]. The prevalence of hip dysplasia in the general population ranges from 4.0 to 12.8% [2, 3]. Research shows that patients with hip dysplasia are 5 times more likely to develop OA than patients with normal hip morphology, eventually requiring a hip replacement [4]. More broadly, hip dysplasia has a long history of association with OA [5] and is considered the leading precursor to OA across North America [6–8] and Europe [9, 10]. Wylie and Peters have established a clear relationship between the severity of deformity (as per radiological findings) and risk for OA development [5]. The more shallow acetabulum results in a smaller surface area of cartilage for weight bearing and leads to overload of the acetabular rim and labrum [11]. This leads to progressive damage of the cartilage in the hip joint and eventually causes arthritic changes [6], as demonstrated by Kim et al.’s correlation between lack of proteoglycan content and severity of arthritic symptoms [12]. Prior to the development of advanced OA, patients often have a prolonged phase of painful hip symptoms that interfere with activity and quality of life [13, 14]. These symptoms usually affect younger adult patients, who will require a hip replacement surgery if not treated for their dysplasia [13]. Fortunately, hip dysplasia can be diagnosed before more severe damage occurs and treated through hip preservation surgery (including periacetabular osteotomy) [6].

The Bernese periacetabular osteotomy (PAO) reorients the more shallow and vertically oriented acetabulum and has been used successfully for over 30 years as the standard of care for hip dysplasia [15]. Garbuz et al. showed that hip dysplasia significantly affects quality of life and that surgical correction with PAO leads to a significant improvement [14]. In addition, PAO has been shown to limit radiographic changes in 88% and 75% of hips at 10- and 20-year follow-ups respectively [16, 17]. The optimization of joint surface area in the weight-bearing region of the hip and improvements in the mechanical advantage of the abductor musculature are thought to provide most of the symptomatic improvement post-operatively. PAO outcomes have shown good symptomatic improvements, low complication rates, and an 18-year hip joint survival of 74% [18], whereas patients with untreated hip dysplasia have shown a 20-year hip joint survival of 33% [4]. More recently, Wyles et al. showed that for patients undergoing a PAO for symptomatic dysplasia, the rate and pattern of progression approximated those for patients with normal morphology from the historical cohort as well as significantly improved when compared with patients with unmanaged DDH. Similarly, in patients with Tönnis grade 1, the probability of progression to total hip arthroplasty at 5 and 10 years was 2% and 11%, respectively, compared with 23% and 53%.

A PAO is not only recommended to *delay or prevent* the need for joint replacement surgery later on in life [10, 19], but *positively impact the quality of life* in patients with hip dysplasia. By doing a PAO, we can offset the need for a future hip replacement, which also saves money, as a PAO has been demonstrated as a more cost-effective procedure than a total hip replacement [20].

Despite the breadth and depth of evidence highlighting the benefits following a PAO, 60–85% of patients have concomitant intraarticular pathology (cartilage damage) that cannot be corrected with a PAO [21, 22] and 11% continue to exhibit symptoms post-surgery [23]. Patients with hip dysplasia commonly have concomitant labral tears [24–26], which has been suggested to be responsible for residual symptoms after PAO [27]. Although MRIs have been routinely used to identify intraarticular pathology, they have been shown to be unreliable to appropriately detect them and quantify their severity [28]. A hip arthroscopy, performed using a small camera, allows surgeons to address the intraarticular pathology inside the hip joint. As a result, some have advocated combining arthroscopic labral re-fixation/debridement and PAO [29–31]. Between 2006 and 2010, there has been a 600% increase in hip arthroscopies in the USA [32], with similar trends in Canada, demonstrating its high uptake since the mid-2000s. Although hip arthroscopy allows the surgeon to potentially address other intraarticular pathologies (i.e., ligamentum teres, chondral injuries), the effect of arthroscopic management of these injuries concomitantly with PAO is unknown. Furthermore, it is unknown whether cartilage damage can be mitigated with the addition of an arthroscopic procedure [33]. Due to additional operative time, equipment, and human resources, costs are substantially increased by adding an arthroscopy to a PAO [34, 35]. In Ontario, the addition of hip arthroscopy to the PAO represents a 125% increase in cost just in the OR [36]. While the cost-effectiveness of a PAO has been established in the US healthcare (cost-effectiveness of $7856 per quality-adjusted life year and an average incremental effectiveness of 0.15) [20], a true cost-utility benefit must be demonstrated if arthroscopic management of labral and other intraarticular pathologies can be justified in these patients.

## Methods/design

### Principal research questions

The primary objective of this project is to assess the impact of concomitant hip arthroscopy with PAO for patients with symptomatic hip dysplasia on quality of life and cartilage health when compared to patients undergoing PAO only. The secondary objective is to investigate the cost utility of performing arthroscopy with a PAO from a healthcare utilization and societal perspective.

Our hypothesis is that concomitant hip arthroscopy at the time of PAO to address intraarticular pathology will result in significant improvements in quality of life and prevent further cartilage damage when compared to PAO alone. Also, we hypothesize that the additional costs associated with hip arthroscopy will be offset by greater clinical improvements and decreased cost consequences in this group and that combined hip arthroscopy and PAO will prove to be a cost-effective procedure.

### The need for a trial

Dysplasia of the hip is one of the main causes of secondary OA [6–10]. Literature has demonstrated that PAO effectively alters the progression of hip dysplasia [19]. Over the past 3 years, there have been three systematic reviews looking at the clinical impact of arthroscopy for hip dysplasia, with all concluding potential benefits of the procedure from pre-experimental studies, but highlighting the absence of randomized controlled trials limiting the utility of the results [37–39]. Furthermore, there have been two systematic reviews looking at the contribution of arthroscopy, PAO, or a combination of both procedures in patients with hip dysplasia, both concluding the lack of robust studies concerning the combination of the two procedures [40, 41].

According to the 2019 systematic review [39], there have been four studies looking at the clinical benefit of addressing labral and/or other intraarticular pathology at the time of PAO for hip dysplasia. All of these studies have been non-randomized cohorts [22, 30, 42, 43], so the true magnitude of clinical benefit from the combined interventions has been impossible to determine. Three of these studies saw clinical benefits when adding arthroscopy to PAO, while the fourth did not. The last study involved an additional intervention (osteochondroplasty), rendering the isolation of arthroscopic labral refixation/debridement as a possible benefit difficult. In addition to their pre-experimental design, the other three studies demonstrating positive results also possess serious biases limiting the validity of the results, such as low sample sizes, inequivalent groups at baseline, patient allocation bias, and lack of standardization of co-interventions. Thus, the role labral refixation/debridement played in the eventual outcome in addition to PAO remains uncertain.

Additionally, no study to date has conducted a cost-effectiveness analysis comparing the two surgical treatment strategies. Two studies were recently conducted in the USA comparing the cost-effectiveness of hip arthroscopy compared to non-operative management of labral tears in young adults [44, 45], while both studies found that although there is an added cost to perform hip arthroscopies, it was more cost-effective compared to non-operative management. Furthermore, no study to date has compared the cost-effectiveness of periacetabular osteotomy with and without hip arthroscopy, in relation to patient quality of life. As hip arthroscopy is a relatively new procedure and even more so as adjunct to the PAO, it is critical to demonstrate its benefits to patient outcome as well as cartilage health.

### Proposed trial design

The proposed trial design follows the same design as our completed feasibility pilot trial, to which we began recruiting in January 2019. Logistical and protocol issues have been addressed and resolved through close collaboration between the clinical research coordinators and surgeons to ensure a streamlined approach. As such, we are set up to efficiently and effectively conduct a multisite randomized, parallel group superiority trial with two sites in Canada (The Ottawa Hospital and Centre Hospitalier Universitaire de Québec) and two sites in the USA (William Beaumont Hospital in Detroit and Washington University in St Louis).

### Planned trial interventions

All patients will undergo a Bernese periacetabular osteotomy (PAO) as the standard of care for treatment of symptomatic hip dysplasia/hip instability. The PAO will be completed by the treating surgeon’s usual technique using a rectus femoris-sparing approach. All surgeons have over 10 years of experience with both techniques of hip arthroscopy and PAO as stand-alone procedures and thus are past the learning curve for both procedures. After completion of the PAO, the patient’s range of motion will be assessed intra-operatively. Once optimal correction is achieved with PAO, a range of motion of the hip is done, and if flexion less than 100° is achieved and/or less than 20° of internal rotation at 90° of flexion is achieved, the surgeon will relieve the impingement at either the sub-spine area, i.e., anterior inferior iliac spine, or the femoral head/neck junction through an anterior arthrotomy (Additional file 2).

All patients will receive standardized DVT prophylaxis and standardized heterotopic ossification prophylaxis with non-steroidal anti-inflammatory medications (NSAIDS) for a minimum of 10 days post-operatively unless medical contra-indications exist. Protected weight bearing on the operative leg will be applied for a minimum of 6 weeks post-operatively [46]. After this period, all patients will undergo a standardized exercise protocol to be accomplished at home following these guidelines [47]: standing open-chain active hip abduction and flexion and knee extension sitting. These exercises will be performed for 2 weeks. For the following 2 weeks, step up/step down and side-stepping (with resistance band) will be accomplished. All exercises will be performed every other day, with three sets of 10 repetitions. Patients will be asked to complete an exercise diary to assess and promote adherence (Additional file 3). Patients will be instructed to contact their treating surgeon if they experience prolonged pain or discomfort after exercise.

Physical examination and radiographic follow-up assessments and measurements will be performed at regular intervals until the PAO has completely healed as part as standard of care. Radiographic control (well-centered AP pelvis and 45° Dunn view) done at the pre-operative time point, 2–4 weeks, 6 months, 12 months, and 24 months post-operatively, is the current standard of care at all institutions involved in the study [48]. Additional x-rays may be performed at the surgeon’s discretion. In addition to the standard of care treatment described above, patients will be randomized to either the *experimental group* or the *control group.*

Patients randomized to the *experimental group* will undergo central compartment hip arthroscopy prior to completion of the PAO. Diagnostic arthroscopy will first be performed, and intra-operative findings will be recorded on a standardized reporting form (Additional file 4). Hip arthroscopy will be carried out using the treating surgeon’s usual technique and will adhere to the following guidelines: a limited inter-portal capsulotomy may be made to allow sufficient space for visualization and instrumentation, if needed (a “T” capsulotomy should not be performed); labral refixation using a minimum of two suture anchors for any identified unstable labral tears; labral debridement should be reserved for only clearly irreparable tears or very small, stable tears; maximal preservation of any remaining intact labral tissue should be attempted; treatment of chondral lesions and ligamentum teres pathology may be performed at the surgeon’s discretion; and arthroscopic cam decompression should not be performed (Additional file 2). Patients randomized to the *control group* will undergo isolated PAO.

### Randomization

Randomization will be carried out in blocks randomly varying between 2 and 4 to ensure equal numbers in both treatment arms (i.e., “PAO” and “Scope-PAO”). Randomization will be stratified by recruiting site to allow for even distribution of intervention covariates and patient characteristics across each site and by sex to ensure adequate distribution of this variable for the analyses. Patients will be randomized just after enrolment, because MRI sensitivity is inadequate to identify intraarticular pathologies [28]. This will allow the surgeon’s office and treating institution to appropriately plan for the required surgical intervention, necessary equipment, operating room time, etc. Patients will be randomized through an on-line computer randomization program that will be accessible by designated research staff from all participating sites.

### Proposed methods for protecting against sources of bias

The addition of hip arthroscopy represents a discrete intervention added on to the current standard of care for treatment of symptomatic hip dysplasia (i.e., PAO). Thus, a randomized trial represents the best study design for assessing its potential additive effect. Since the treating surgeon must administer the experimental intervention, a double-blind design is not possible.

Assessments that are not patient self-report and data analyses will be performed blinded to allocation. When submitting our feasibility protocol to our Research Ethics Board in the spring of 2018, we initially had indicated blinding of study participants through a diagnostic arthroscopy in the PAO-only patients (same incision as PAO+arthroscopy group). However, there were ethical implications with inserting a scope into the hip of the control group and therefore we converted the study design to a single-blinded methodology only, recognizing that this may introduce a potential source of bias in any patient-reported outcome measures. In addition to patient-reported outcomes, objective performance measurements, administered by blinded assessors, will be performed as one of the outcome measures. At each postoperative time point, patients will document through a standardized form conservative and surgical co-interventions targeting the treated hip and received after the previous time point.

### Inclusion criteria

Skeletally mature patient undergoing Bernese PAO for symptomatic acetabular dysplasia/hip instability, as defined by [name] et al.’s validated Ottawa Classification for Symptomatic Acetabular Dysplasia [49]Patients having over 6 months of non-surgical management including physical therapy and NSAIDsBetween 16 and 50 years oldPatient capable of giving informed consent to participate

### Exclusion criteria

PregnancyPrior hip/pelvis surgery of any kind on the surgical sidePrior hip arthroplasty surgery on either sideConcurrent proximal femoral osteotomy and/or surgical hip dislocationRadiographic evidence of arthritis (i.e., Tönnis grade ≥ 2)Systemic inflammatory diseaseKnown connective tissue disorder (e.g., Ehlers-Danlos syndrome)Known neuromuscular disorder (e.g., cerebral palsy, spina bifida)Known skeletal dysplasia (e.g., achondroplasia, multiple epiphyseal dysplasia)Cognitive impairment (individuals who, based on the treating surgeon’s assessment during the pre-operative discussion, are incapable of providing informed consent for treatment. In other words, if the patient requires a substitute decision maker to consent to surgery on their behalf, they would be excluded from study participation)Patient unable/unwilling to complete all required follow-up visitsPatient unwilling to participate

### Primary outcome measure

#### iHOT-33

Disease-specific patient-reported quality of life will be the primary outcome used for comparison between the two treatment groups as measured by the International Hip Outcome Tool (iHOT-33). The iHOT-33 is a reliable, validated, self-administered quality of life assessment tool for young, active patients with hip symptoms [50]. The iHOT-33 is a core measure for this patient population [51, 52]. Patients will complete this questionnaire pre-operatively and at the following time intervals post-operatively: 6 months, 12 months (primary time point), and 24 months (Additional file 5). The value of the iHOT-33 at each time point will be used for analysis. Data will be aggregated such that the mean scores in each treatment group will be compared at each time point. In addition, the proportion of patients in each treatment group that have an increase in their score greater the minimum clinically important difference (MCID) of the score will be compared.

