### Health economic measures

A cost-utility analysis will be performed to compare costs and quality-adjusted life years (QALYs) associated with the intervention and the standard of care over a 24-month period. The analysis will be conducted from the perspective of Canada’s publicly funded healthcare system, and resource use will be measured via a retrospective chart review. Only Canadian sites will be included in the economic analysis because of the important differences in healthcare systems between countries, with general consensus among health economists that power issues do not apply to these types of analyses. We will include the intervention costs (i.e., PAO and arthroscopy procedure) and health utilization-related costs. Health utility scores will be derived from the PROMIS score for each trial participant using a validated algorithm [62]. QALYs will be estimated using the total area under the curve method [63]. The statistical analysis will be conducted in accordance with current guidelines for clinical and cost-effectiveness analysis alongside RCTs [64]. The incremental cost and QALY will be estimated using generalized estimating equations that explicitly allows for the modeling of normal and non-normal distributional forms of repeated measure data. The cost per QALY gained will be obtained through the difference in average costs of the two treatment options divided by the difference in average QALYs as denoted by the coefficient of the therapy indicator variables. Uncertainty in the analysis will be addressed by estimating 95% confidence intervals using a non-parametric bootstrapping method. As a secondary analysis, we will use a societal perspective and consider productivity loss as measured through the work productivity and activity impairment questionnaire (WPAI:SHP) (completed at 6, 12, and 24 months), which has been used in studying patients after elective orthopedic surgery [65] (Additional file 9).

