### Analyses and frequency of analyses

The analysis will be conducted on an intention-to-treat basis. Statistical analyses will be performed blinded to treatment allocation. A level of significance of 0.05 will be used for all analyses. The underlying assumptions of all statistical procedures will be evaluated, and data transformation will be considered. Using descriptive statistics, baseline patient characteristic differences between the study groups will be assessed (age, sex, outcomes) and differences will be controlled for in the statistical analyses. Repeated measures mixed models and general linear mixed models will be used for handling continuous and dichotomous outcomes respectively. Sex will be specifically assessed as an effect modifier in the analyses. Multiple imputation will be considered as a sensitivity analysis.

For cartilage health, the biochemical content of the cartilage will be evaluated using MRI T1ρ mapping. The scan will be performed pre- and 2 years after surgery using a 3D turbo spin echo acquisition method with T1ρ preparation (CUBE QUANT) and the following parameters: TR = 1350 ms, TEeff = 40 ms, FOV = 25.6 × 25.6 cm^2^, in-plane resolution = 0.5 × 0.5 mm^2^, slice thickness = 3 mm, number of slices = 32 slices, no slice gap (3D sequence), B1 = 500 Hz, spin-lock times = 1, 15, 30, 45 ms, and scan time = 18 min [56, 71] (Additional file 1, Figure 3). For post-pressing, T1ρ-weighted datasets will be co-registered to the proton density-weighted turbo spin echo images and analyses described in our previous publications [57, 70]. The hip cartilage will be divided in six regions of interest (ROIs): anterior lateral, anterior middle, anterior medial, posterior lateral, posterior middle, and posterior lateral for regional proteoglycan assessment [57]. T1ρ values from the different cartilage regions will be compared and evaluated for significant differences between the pre-operative and the follow-up scan using repeated measures analysis of variance (ANOVA).

In addition to the final analysis, an interim analysis will be performed after 2.5 years to determine if the study must be terminated. This will be based on the following results: serious adverse events significantly higher in the experimental group, greater than expected beneficial effects, improbable statistically significant difference by the end of the study, and participant recruitment is severely lagging and unlikely to achieve the target.

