### Anticipated compliance problems

We do not anticipate compliance problems, as the interventions are one-time surgeries. If patients cross over from one treatment group to another after randomization, their results will still be included in the final analysis on an intention-to-treat basis. All attempts should be made to avoid patient cross-over and if cross-overs do occur after randomization, the reason for this will be recorded. The aim of the pilot was to test the methods and optimize data collection procedures. If that data is shown to be applicable to the current proposal, it will be included.

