### Risks to safety of study participants

The risk of a PAO performed without hip arthroscopy may lead to untreated labral tears that may result in ongoing pain and require arthroscopy at a later time [60]. The risks of a PAO performed with a hip arthroscopy include the following: increased surgery time, fluid extravasation into the soft tissues resulting in increased hip/leg swelling, traction on the leg possibly increasing the risk of a nerve injury, partial capsulotomy which may lead to hip instability, and inadvertent damage to the labrum or cartilage as well as intra-articular adhesions. Although there are additional risks to performing an arthroscopy in addition to a PAO, it is hypothesized that arthroscopy will address intraarticular pathology, thereby minimizing cartilage damage and improving quality of life.

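### Resource use for the cost-utility analysis comes from retrospective chart review, although the trial already records later surgery and conservative care on the treated hip prospectively

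*Protocol article*

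**What the plan says.** On cost, the protocol article (Health economic measures) plans a 24-month cost-utility analysis at the Canadian sites, covering the index procedures and health-utilization costs. For the source of these data it states that "resource use will be measured via a retrospective chart review". Utilities are derived from each participant's PROMIS score and turned into QALYs by area under the curve.

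On later care, the section on protecting against bias says, for every scheduled visit after surgery, that "patients will document through a standardized form conservative and surgical co-interventions targeting the treated hip and received after the previous time point". The Adverse events section adds a reoperation rate, by group, at 12 and 24 months, using standardized failure modes. The section on risks foresees that PAO without arthroscopy may leave "untreated labral tears that may result in ongoing pain and require arthroscopy at a later time".

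On benefit, the iHOT-33 section says "The value of the iHOT-33 at each time point will be used for analysis". Besides the comparison of means, it compares "the proportion of patients in each treatment group that have an increase in their score greater the minimum clinically important difference (MCID"). The analysis section adds "The analysis will be conducted on an intention-to-treat basis". For patients who cross over after randomization, the compliance section says "their results will still be included in the final analysis on an intention-to-treat basis".

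**The concern.** Cost and benefit of the same later treatment reach the economic analysis by different routes. A patient who has further surgery, imaging or physiotherapy on the hip reports the resulting health state on PROMIS at the scheduled visits, so any gain is counted. The cost is counted only if the care appears in the charts that are reviewed. Care obtained elsewhere would look free.

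This matters because the protocol's economic hypothesis is that the added cost of arthroscopy is offset in part by lower cost consequences afterwards. Those consequences are the events that a retrospective chart review is most likely to lose. Later arthroscopy is named as a possible result of PAO alone, so incomplete capture could make PAO alone look cheaper than it is.

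A related question arises for the responder comparison. A PAO-alone patient who has a later arthroscopy and whose iHOT-33 increase then exceeds the MCID is a responder in the PAO-alone arm. The reoperation rate is reported separately and does not show whether the same patient was also counted as a responder.

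**Working it through.** **Sources set side by side**

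- Chart review: retrospective, and the only source of resource use that the costing section names.
- Co-intervention form: prospective, completed by patients at each postoperative time point, covers surgical and conservative care on the treated hip. Not mentioned in the costing section.
- Reoperation record: by group at 12 and 24 months. Not mentioned in the costing section.
- PROMIS: completed by patients at 6, 12 and 24 months, and the source of utilities and QALYs.

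The QALY side thus depends on the patient's own report. The cost side, as stated, does not.

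**Size on the cost side**

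Inputs: the Background says that adding arthroscopy raises operating-room cost by 125% in Ontario. Let P be the operating-room cost of a PAO, so the increment is 1.25P. The documents give no rate of later arthroscopy. I assume r = 2%, 5% or 11%; the last is the Background's figure for continuing symptoms after PAO, used as a high value and not as a reoperation rate. I also assume that a later arthroscopy costs about 1.25P. Let m be the share of such operations that the charts miss, with C for PAO alone and E for the experimental arm.

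Error in incremental cost (experimental minus control) = 1.25P × (r_C·m_C − r_E·m_E)

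Extreme case, all missed in control and none in the experimental arm (m_C = 1, r_E·m_E = 0):

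- r_C = 2%: 0.02 × 1.25 = 2.5% of P per control patient
- r_C = 5%: 0.05 × 1.25 = 6.25% of P
- r_C = 11%: 0.11 × 1.25 = 13.75% of P

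As a share of the 1.25P increment these are 2%, 5% and 11%. With half missed they halve. If r·m is equal in the arms, the net error is zero; if it is larger in the experimental arm, the sign reverses. Conservative care cannot be sized from the documents.

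The number of Canadian participants is not given. If recruitment follows the stated PAO volumes (two sites at 40 a year out of 200 in all), the Canadian share is 80/200 = 40%, so 0.40 × 126 = 50.4, or about 25 per arm. The three rates then mean 25 × r = 0.5, 1.25 and 2.75 later arthroscopies in the PAO-alone arm.

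**Size on the responder side**

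The planned 63 per group reproduces closely: with difference 10, SD 16, two-sided alpha 0.05 and power 0.90, the non-central t gives 55 evaluable per group, and 55 × 1.15 = 63.25. After 15% loss, 63 × 0.85 = 53.55, about 54 per group.

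Counting patients with later surgery as non-responders lowers an arm's responder proportion by r × s, where s is the share of them above the MCID. With s assumed between 50% and 100%:

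- r = 2%: 1.0 to 2.0 points (0.5 to 1.1 of 54 patients)
- r = 5%: 2.5 to 5.0 points (1.4 to 2.7 of 54)
- r = 11%: 5.5 to 11.0 points (3.0 to 5.9 of 54)

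These are one-arm figures. The effect on the comparison is r_C·s_C − r_E·s_E, which is zero when the products are equal.

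**The case against.** The strongest case on the other side has four parts.

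- **Scores after later surgery.** Using the observed score whatever happened in between is a coherent treatment-policy comparison of two strategies, each with later care as needed. A PAO-alone patient who does well after a later arthroscopy is a valid outcome of that strategy. This stands, and it is why the stated responder analysis should not be replaced. A composite definition would also import a decision by an unblinded surgeon: greater willingness to scope hips never scoped before would itself create control failures.
- **Visibility.** Later surgery is not hidden. It is on the co-intervention form and in the reoperation rates by group. This stands too, but it makes the costing gap easier to close.
- **Direction.** The Adverse events section cites a retrospective review with no difference in reoperation rates, although it notes selection bias. The section on risks lists possible harms of arthroscopy as well. Missed care could fall in either arm. This stands: the direction is plausible but not shown.
- **Silence in an article.** The costing section does not say that charts are the sole source, and the abstract lists health services utilization among the data collected. A fuller document might link the records. This stands only in part, because the section does state how resource use is measured, and the choice of data source belongs in the protocol.

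A reader might infer more: that every PAO-alone patient with a later arthroscopy is counted as a success, or that the responder result is biased toward PAO alone. The documents support neither. Such a patient is a responder only if the score rises by more than the MCID, the rule is the same in both arms, and no rate of later surgery is given for either.

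**Conclusion.** The point holds for the costing. The stated method lets the benefit of later care into the QALYs unconditionally and its cost only through the charts, while better-timed records of the same care go unmentioned. In the extreme case the control arm's cost is understated by about 2.5% to 14% of a PAO's operating-room cost per patient. That range rests on assumed rates of 2% to 11%, on complete non-capture in one arm only, and on a later arthroscopy costing about the quoted increment. The true net error could be zero or of either sign. Only the Canadian economic analysis is affected.

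The score-only responder definition is not an error. It leaves open how much of each arm's response was reached after further surgery, which a supplementary analysis can show. The primary comparison of mean iHOT-33 at 12 months is unaffected. No view is taken on when later surgery should be offered.

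**What to change.** In Health economic measures, state that for Canadian participants the patient co-intervention form and the reoperation record are additional sources of resource use beside chart review, and that discrepancies with the charts are queried. The cost is a data merge and some queries; the data are already being collected.

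In the iHOT-33 section, keep the score-only MCID comparison under intention-to-treat. Add one supplementary responder analysis, applied to both arms, in which a patient with further surgery on the treated hip before the time point counts as a non-responder. Name which of the standardized failure modes in the Adverse events section count, and note that the decision to reoperate is unblinded. The cost is one extra analysis, with responder rates that will be the same or lower and must be read with that caveat. The mean-score analysis needs no change.
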